## 2. ABBREVIATIONS

|         |                                                             |
|---------|-------------------------------------------------------------|
| 21 CFR  | Title 21 of the Code of Federal Regulations                 |
| AAQ-II  | Acceptance in Action Questionnaire                          |
| AE      | Adverse Event                                               |
| AUDIT   | Alcohol Use Disorders Identification Test                   |
| BDI     | Beck Depression Inventory                                   |
| BP      | Binding Potential                                           |
| CBC     | Complete Blood Count                                        |
| CGI-I   | Clinical Global Impression - Improvement                    |
| CIOMS   | Council for International Organizations of Medical Sciences |
| CLEAR   | Client Language Easy Reading                                |
| CRF     | Case Report Form                                            |
| d       | Cohen's d                                                   |
| DBS     | Deep Brain Stimulation                                      |
| DUDIT   | Drug Use Disorders Identification Test                      |
| EBI     | Emotional Breakthrough Inventory                            |
| ECG     | Electrocardiogram                                           |
| ECT     | Electroconvulsive Therapy                                   |
| EDC     | Electronic Data Capture                                     |
| EQ-5D   | Euro Qual 5 Dimensions                                      |
| FDA     | Food and Drug Administration                                |
| FSH     | Follicle Stimulating Hormone                                |
| g       | Hedges g                                                    |
| GCP     | Good Clinical Practice                                      |
| HADS    | Hospital Anxiety and Depression Scale                       |
| HAM-D   | Hamilton Depression Scale                                   |
| HDPE    | High-Density Polyethylene                                   |
| Hopkins | Johns Hopkins University                                    |
| HPMC    | Hydroxypropyl Methylcellulose                               |
| HPPD    | Hallucinogen-Persisting Perception Disorder                 |
| HR      | Heart Rate                                                  |
| Hrs     | Hours                                                       |
| HRT     | Hormonal Replacement Therapy                                |
| ICD-10  | International Classification of Disorders - 10              |
| ICF     | Informed Consent Form                                       |
| ICH     | International Conference on Harmonization                   |
| IND     | Investigational New Drug                                    |
| IP      | Investigational Product                                     |
| IRB     | Institutional Review Board                                  |
| ISF     | Investigator Site File                                      |
| IUD     | Intrauterine Device                                         |
| IUS     | Intrauterine Hormone-releasing System                       |
| LEQ     | Lasting Effects Questionnaire                               |
| LSD     | Lysergic Acid Diethylamide                                  |
| MADRS   | Montgomery-Asberg Depression Rating Scale                   |
| MADRS-S | Montgomery-Asberg Depression Rating Scale- Self rating      |

|        |                                               |
|--------|-----------------------------------------------|
| MAOIs  | Monoamine Oxidase Inhibitors                  |
| MBq    | Mega-Becquerel                                |
| MD     | Medical Doctor                                |
| MDD    | Major Depressive Disorder                     |
| MDMA   | 3,4-Methylenedioxy-methamphetamine            |
| MedDRA | Medical Dictionary for Regulatory Activities  |
| MEQ-30 | Mystical Experience Questionnaire             |
| mmHg   | Millimeters of Mercury                        |
| MMRM   | Mixed Model for Repeated Measures             |
| MPA    | Medical Products Agency                       |
| MRI    | Magnetic Resonance Imaging                    |
| MRS    | Magnetic Resonance Spectroscopy               |
| NYU    | New York University                           |
| p      | Probability                                   |
| PCP    | Phencyclidine                                 |
| PET    | Positron Emission Tomography                  |
| PI     | Principal Investigator                        |
| ROI    | Region(s) of Interest                         |
| SAE    | Serious Adverse Event                         |
| SAEs   | Serious Adverse Events                        |
| SAP    | Statistical Analysis Plan                     |
| SaS    | Set and Setting Protocol                      |
| SDS    | Sheehan Disability Scale                      |
| SNRIs  | Serotonin-norepinephrine reuptake inhibitors  |
| SOP    | Standard Operating Procedure                  |
| SPIR   | Subjective Psychedelic Intensity Rating       |
| SSRIs  | Selective Serotonin Reuptake Inhibitors       |
| SUSAR  | Suspected Unexpected Serious Adverse Reaction |
| TAC    | Time Activity Curve                           |
| TCAs   | Tricyclic Agents                              |
| TEAE   | Treatment Emergent Adverse Event              |
| THC    | Tetrahydrocannabinol                          |
| TIA    | Transient Ischemic Attack                     |
| TMS    | Transcranial Magnetic Stimulation             |
| TRD    | Treatment-Resistant Depression                |
| TSH    | Thyroid Stimulating Hormone                   |
| VNS    | Vagus Nerve Stimulation                       |
| WOCBP  | Woman of Childbearing Potential               |

### 3. PROTOCOL SYNOPSIS

**Title**

The effect of psilocybin on MDD symptom severity and synaptic density – a single dose randomized, double blind, placebo-controlled phase 2b positron emission tomography study

**Study Code**

PSIPET

**Name of Sponsor**

SLSO

Organisationsnr: 232100-0016

**Medical Monitor**

Inspira Medical AB

**Phase of Study**

Phase 2b

**Sample Size**

30 randomized

**Name of Investigational Product (IP)**

Psilocybin, 3-[2-(dimethylamino)ethyl]-1H-indol-4-yl] dihydrogen phosphate

**Name of Active Placebo**

Niacin

**EudraCT**

2020-002790-94

**Description of IP and Active Placebo**

|                                 |                                                                                                                                                                                                                          |                                                      |
|---------------------------------|--------------------------------------------------------------------------------------------------------------------------------------------------------------------------------------------------------------------------|------------------------------------------------------|
| Study Intervention Name: | Psilocybin
(active drug product)                                                                                                                                                                                      | Niacin
(active placebo product)                   |
| Dosage formulation:      | One active capsule contains 25 mg of psilocybin                                                                                                                                                                          | One active placebo capsule contains 100 mg of niacin |
| Capsule:                 | Size 2 hydroxypropyl methylcellulose (HPMC), opaque                                                                                                                                                                      | Size 2 HPMC, opaque                                  |
| Unit dose strength:      | 25 mg                                                                                                                                                                                                                    | 100 mg                                               |
| Route of Administration: | Oral (solid dose)                                                                                                                                                                                                        | Oral (solid dose)                                    |
| Dosing instructions:     | One capsule administered with water                                                                                                                                                                                      | One capsule administered with water                  |
| Packaging and Labeling:  | Study Intervention will be provided in a high-density polyethylene (HDPE) bottle. Each bottle will contain one capsule (psilocybin or niacin) and will be labeled as required per Swedish requirement for blinded study. |                                                      |

### Study Description and Overview

Thirty participants (males and females) ages 20 to 65 inclusive, who, at Screening, meet ICD-10 criteria for major depressive disorder (MDD), have a current depressive episode of at least 30-day duration, have a Screening Montgomery-Asberg Depression Rating Scale (MADRS) total score  $\geq 22$  and meet all other inclusion/exclusion criteria will be randomized with a 1-to-1 allocation under double-blind conditions to receive a single 25 mg oral dose of psilocybin or a single 100 mg oral dose of niacin. Niacin will serve as an active placebo control that provides an acute physiological response (flushing) that is intended to aid in blinding of intervention allocation. All randomized participants will be included in the Full Analysis Set (FAS) population used in analyzing primary and secondary study endpoints.

Only participants who meet depressive symptom severity criteria at web screening (MADRS self-rating (MADRS-S) score  $\geq 19$ ) and who do not show an unacceptably large degree of symptom improvement between the web screening and in-person screening (indexed by change in MADRS-S (improvement)  $\leq 30\%$  (MADRS representing web screening will be approximated to MADRS-S + 3) will be eligible for randomization. This is to minimize the risk for spontaneous remission before dosing.

Participants deemed eligible following successful completion of all screening assessments including a structural Magnetic Resonance Imaging (MRI) examination will be determined as eligible.

Eligible participants at Baseline will submit cerebrospinal fluid (CSF), submit blood samples, be examined with positron emission tomography (PET) and the radioligand [ $^{11}\text{C}$ ]UCB-J and receive one preparation session (see further below) to be eligible for randomization on Dosing (Day 0) to receive either psilocybin or niacin active-placebo. They will complete follow-up visits on study Day 1, 8, 15, 42 and 365 (within corresponding visit windows). At day 15 the sampling of CSF, blood and [ $^{11}\text{C}$ ]UCB-J PET will be repeated.

After day 42, all participants will be given follow-up visits at Norra Stockholms Psykiatri for up to one year after dosing, to study dedicated physicians or nurses at a frequency determined by the health care professional. If needed to reach/stay in remission, the participants will be provided antidepressant treatment in accordance with the regional guidelines for antidepressant treatment ([https://psykiatristod.se/regionala-wardprogram/depression](https://psykiatristod.se/regionala-vardprogram/depression)). At least monthly the participants will be asked to provide on-line symptom rating data (via 1177.se). At the 365-day visit, symptoms will be evaluated using MADRS, CGI-I and CGI-S. After completing the study (one year or withdrawal), participants will be subject to standard care, including referral in accordance with regional guidelines.

The study outcome measures will be used to assess depressive symptoms, clinical global functioning, functional disability, anxiety symptoms and health-related quality of life. Safety outcome measures will be collected at all assessment time points from the time of consent through the end of study.

To enhance participant safety, the current study proposes to test psilocybin within a “set and setting” (SaS) protocol similar to the protocol that has been used in all modern studies of psilocybin in both diseased and normal healthy populations. The SaS protocol for this study includes: 1) a preparation with session Facilitators (licensed psychologists) prior to dosing; 2) administration of study medications in an aesthetically neutral room under the supervision of two Facilitators who are present throughout the session (with the exception of short, temporary allowances for facilitator breaks; e.g. bathroom breaks); and 3) three post-dose integration sessions during which participants are encouraged to discuss their intervention experience with the Facilitators. To evaluate the Facilitators' adherence to the study manual, and the role of Facilitators' and participants' in-session behaviors for treatment outcome, all five sessions in the trial with Facilitators present will be recorded. The SaS will be identical for those randomized to psilocybin or niacin active placebo.

### **Study Duration**

The planned maximum study duration for each participant will be approximately one year, with variation primarily dependent on the length of the screening period, the number of days between baseline and dosing, and the visit windows provided for each post-dose assessment. For each participant, the study will be divided into two phases: Phase A or treatment phase (day 0 to and including day 42), and phase B or follow-up phase (day 43 – 365).

### **Primary Objective**

The primary objective of this study is to evaluate the efficacy of a single 25 mg oral dose of psilocybin for major depressive disorder (MDD) compared to an active placebo (niacin) in otherwise medically-healthy participants between the ages of 20 and 65, assessed as the difference between groups in changes in depressive symptoms.

### **Primary Outcome Measure**

Change in blinded rater MADRS total score from Baseline to Day 8.

### **Secondary Objective**

One secondary objective is to evaluate the effect of psilocybin on synaptic density in prefrontal cortex and hippocampus, by comparing the change in [C]UCB-J binding after psilocybin and placebo dosing.

The other exploratory objective is to study the clinical effect on depressive symptoms, clinical global impression, perceived disability and of post treatment use of antidepressants.

The following secondary endpoints will be evaluated to support the primary and secondary objectives:

### Secondary Outcome Measures

- Relative increase (ratio) in [C]UCB-J binding from Baseline to Day 15 post dose
- Change in MADRS total score from Baseline to Day 15, 42, 180 and 365 (end of study) respectively
- Change in MADRS total score from Baseline to the treatment period (mean of Day 8-365)
- Change in MADRS-S score from Baseline to Day 365 (end of study)
- Change in MADRS-S score from Baseline to the treatment period (mean of Day 8-365)
- Response rate at all time points post dose (MADRS and MADRS-S)
- Remission rate at all time points post dose (MADRS and MADRS-S)
- Change in Sheehan Disability Scale (SDS) score from Baseline to Day 365 (end of study)
- Change in SDS score from Baseline to the treatment period (mean of Day 8-365)
- Change in Clinical Global Impression (CGI) score from Baseline to Day 8, 42, 180 and 365 (end of study) respectively
- Change in CGI score from Baseline to the treatment period (mean of Day 8-365)
- Time to initiation of antidepressant treatment in follow up phase (day 43-365)

### Exploratory Objectives

One exploratory objective is to evaluate the effect of psilocybin on biological markers of synaptogenesis, neuroinflammation, serotonergic activity and on self-rated depressive symptoms, reversal fear learning, clinical global functioning, anxiety symptoms, functional disability, health-related meaning of/satisfaction with life and psychological flexibility, subjective psychedelic experiences, participants' expectations prior to the/experience of the intervention, and facilitator and participants' in-session behaviors.

The purpose of collecting the exploratory outcome measures is to further understand the effect of psilocybin. The results will be reported in academic journals and not included in the Clinical Study Report.

### Exploratory Outcome Measures (see table 1 for time points)

1. Biomarkers
  - 1.1. fMRI BOLD signal
  - 1.2. fMRI activation paradigms post dosing
  - 1.3. p11 (blood)
  - 1.4. BDNF and VEGF (plasma)
  - 1.5. monoamines and monoamine metabolites (CSF)

- 1.6. cytokines (CSF)
- 1.7. kynurenic acid and metabolites (CSF)
2. Scales
  - 2.1. General Anxiety Disorder 7 (GAD-7)
  - 2.2. Euroqol five dimension five level (E-5D-5L)
  - 2.3. Euroqol visual analogue scale (EQ-VAS)
  - 2.4. Mystical Experience Questionnaire (MEQ)
  - 2.5. Emotional Breakthrough Inventory (EBI)
  - 2.6. Challenging Experience Questionnaire (CEQ)
  - 2.7. Lasting Effects Questionnaire (LEQ)
  - 2.8. Treatment Expectation and Evaluation questionnaires
  - 2.9. Meaning of Life Questionnaire (MLQ)
  - 2.10. Satisfaction with Life Scale (SWLS)
  - 2.11. Acceptance in Action Questionnaire (AAQ-II)
  - 2.12. The Actively Living and Interconnecting Vitality in one's Embedded-world (ALIVE) Questionnaire
  - 2.13. Working Alliance Inventory-Short (WAI-S)
  - 2.14. Motivational Interviewing Treatment Integrity Code (MITI)
  - 2.15. Client Language Easy Rating (CLEAR)
  - 2.16. Scale for Psychedelic Intensity Rating (SPIR)

### Safety Objectives

The overall safety objective of this study is to evaluate a single 25 mg oral dose of psilocybin compared to an active placebo in incidence, severity and frequency of Adverse Events (AEs), Treatment Emergent AEs (TEAEs), and Serious Adverse Events (SAEs) during and after the dosing session and at all follow-up visits. Solicited AEs will be compared from randomization until day 8 only.

### Solicited Adverse Events

The following solicited AEs will be collected from randomization to Day 8:

Visual perceptual effects will be solicited by asking the following questions: 1) *Since your dosing session have you experienced any uncontrolled or disturbing return of study drug effects?*, and 2) *Since your dosing session have you experienced any visual distortions (e.g. geometric hallucinations, false perceptions of movement in the peripheral visual fields, flashes of color, intensified color, trails for images of moving objects, positive after-images, halos around objects)?* If a participant reports "Yes" to any of the above questions a study psychologist or psychiatrist will follow up for further assessment/diagnosis.

Additional solicited AEs include:

- Headache
- Nausea
- Elevated blood pressure (BP) as defined by systolic blood pressure (SBP) >140 mmHg or diastolic blood pressure (DBP) >90 mmHg on three separate readings and requiring medication (recorded for Periods 1-2; may result in early termination); and
- Elevated heart rate (HR) as defined as >100 beats per minute (BPM) lasting > 1 hour.

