### 5.5.6 Challenging Experience Questionnaire (CEQ)

CEQ is a validated 26-item self-report scale developed in 2016 to measure acute adverse psychological reactions to psilocybin and other classic hallucinogens. At the end of the dosing session, participants rate the degree to which at any time during that session they experienced potential adverse symptom on a scale from 0 (none; not at all) to 5 (extreme; more than ever before in my life).

CEQ will be administered by the Facilitators on paper and then transferred to the eCRF by study personnel, upon completion of the dosing session when all behavioral effects of the intervention have resolved.

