#### Session Facilitators

Facilitators will be licensed psychologists with experience in the psychological treatment of MDD. Both Lead and Co-Facilitators will have adequate training to identify safety issues during the participant's preparation, dosing, and integration sessions, and will have undergone specific Clinical Facilitator training.

For the majority of the dosing session, both Facilitators will be present in the session room and will attend to the participant. At least one Facilitator will always be present in the session room to continuously observe and evaluate the participant's physical and mental status (allowing for infrequent, short breaks; e.g. facilitator bathroom breaks). Continuous supervision provides a safety structure and ensures that the participant will receive reassurance and emotional support from the Facilitators; should he/she experience strong emotions or become anxious or agitated during the session. Specific dosing session safety monitoring, via eCRF, will be conducted at regular, pre-specified times through assessment of the following: nausea, acute physical or psychological distress, including self-harm, and self-reported anxiety. This is intended to provide Facilitators with an enhanced ability to monitor participant safety and communicate any observed symptoms to the Study Physician, who will determine if immediate clinical assessment is warranted.

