### **17.1 Risks Associated with Psilocybin**

#### **17.1.1 Physiological and Psychological Adverse Effects**

The clinical safety of psilocybin has been extensively studied, both as a single agent and as adjunctive treatment in adult populations. Psilocybin is administered orally, and has been studied in open-label, and double-blind, controlled trials. Dosing regimens have ranged from 0.014 mg/kg to 0.6 mg/kg, administered as either a single dose, or multiple doses weeks apart.

Adverse event data from previous clinical trials has been used to evaluate the physiological profile of psilocybin. The IB for psilocybin summarizes the adverse event data collected from controlled clinical trials utilizing psilocybin in conjunction with cognitive enhancement therapy across multiple subpopulations.

The most likely potential acute adverse effects of psilocybin has been shown to be anxiety, as well as panic, delusion, and cognitive impairments, particularly at higher doses (> 25 mg oral psilocybin) during the period of acute drug action. Such transient episodes of fear or anxiety respond well to verbal reassurance and have not required pharmacological intervention. In previous clinical experience, acute psychological events were resolved by the end of the dosing day.

Overall, the most commonly reported physiological adverse events associated with psilocybin are:

- cardiovascular changes (including increased blood pressure and heart rate)
- nausea
- headache

These adverse events were generally classified as mild to moderate and were found to be transient in nature. No psilocybin-related serious adverse events were reported.

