### 18.1.3 Solicited Adverse Events

The following solicited AEs will be collected:

Visual perceptual effects (Periods 3-4) will be solicited by asking the following questions: 1) *Since your dosing session have you experienced any uncontrolled or disturbing return of study drug effects?*, and 2) *Since your dosing session have you experienced any visual distortions (e.g. geometric hallucinations, false perceptions of movement in the peripheral visual fields, flashes of color, intensified color, trails for images of moving objects, positive after-images, halos around objects)?* If a participant reports “Yes” to any of the above questions a study psychologist or psychiatrist will follow up for further assessment/diagnosis.

Additional solicited AEs include:

- Active suicidal ideation identified through MADRS and verified by clinical assessment.
- Headache; and
- Nausea and
- Elevated blood pressure (BP) as defined by systolic blood pressure (SBP) >140 mmHg or diastolic blood pressure (DBP) >90 mmHg on three separate readings and requiring medication; and

- Elevated heart rate (HR) as defined as >100 beats per minute (BPM) and requiring medication; and
- Drug and alcohol abuse/misuse as defined by the MINI; substance and alcohol use disorders as defined by the MINI; or drug overdose with suicidal intent.

Monitoring for suicidality will be ongoing throughout the duration of the study using MADRS. If at any time during an evaluation or follow up there is concern a participant is suicidal study staff will follow standard of care procedures for managing suicidality, eg as described in <https://psykiatristod.se/regionala-varldprogram/depression>.

To assess for headache after psilocybin administration, participants will be asked if they have or experienced a headache during Period 3, and these will be classified as a migraine, tension headache, or other headache. On the dosing day, participants reporting headache will be encouraged to take non-steroidal anti-inflammatory agents or acetaminophen at home, if needed.

Visual perceptual effects, suicidal ideation verified by clinical assessment, headache, nausea, and overdose with suicidal intent will be reported through normal AE/SAE mechanisms.

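### The acute psychological effects the protocol calls most likely are not solicited adverse events, and the data that would capture them feed no safety endpoint

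*Protocol*

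**What the plan says.** Protocol section 17.1.1 separates two groups of acute harm. On the psychological side it states: "The most likely potential acute adverse effects of psilocybin has been shown to be anxiety, as well as panic, delusion, and cognitive impairments". The same sentence adds that this applies especially at doses above 25 mg, and the section describes such episodes as transient, responsive to reassurance and over by the end of the dosing day. On the physiological side it names cardiovascular changes (blood pressure and heart rate), nausea and headache.

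There are two solicited-AE lists:
- The synopsis, under "The following solicited AEs will be collected from randomization to Day 8", gives visual perceptual effects, headache, nausea, elevated blood pressure and elevated heart rate.
- Section 18.1.3 has these items and adds "Active suicidal ideation identified through MADRS and verified by clinical assessment", together with drug and alcohol misuse and overdose with suicidal intent.

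Two other sources bear on acute psychological harm:
- Section 9.3.2 (Session Facilitators) says "Specific dosing session safety monitoring, via eCRF, will be conducted at regular, pre-specified times", covering "nausea, acute physical or psychological distress, including self-harm, and self-reported anxiety".
- Section 5.5.6 describes the CEQ as developed "to measure acute adverse psychological reactions to psilocybin and other classic hallucinogens". The synopsis lists it as exploratory measure 2.6 and says of the exploratory measures: "The results will be reported in academic journals and not included in the Clinical Study Report".

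Section 5.4.2 sets seven safety endpoints, built from AEs, TEAEs, solicited AEs and SAEs. The statistical analysis plan (3.4 and 5.7) keeps five of them and lists no solicited AEs.

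**The concern.** A solicited list exists so that every participant in both arms is asked the same question about the harms that are expected. Here it does this for the physiological effects and not for the psychological ones, which the protocol itself ranks first. The by-arm incidence of solicited AEs in section 5.4.2 therefore cannot show the effect thought most likely.

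Recording of anxiety, panic, delusion or confusion is left to whoever observes or hears of it and decides that it is an adverse event and not part of the session. That matters more than usual in this trial. Section 9.10 accepts that Facilitators may become functionally unblinded by what they see, so a discretionary decision to record may differ by arm. Events that settle with reassurance on the same day are also the easiest to leave unlogged.

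**Working it through.** No stated figure is involved, so the check sets the sections side by side.

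**Step 1. Effects named in 17.1.1 against the places that ask about them**

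| Effect | Synopsis list | 18.1.3 list | Timed eCRF check, 9.3.2 |
|---|---|---|---|
| Anxiety | no | no | yes, self-reported |
| Panic | no | no | only through general distress |
| Delusion | no | no | no named item |
| Cognitive impairment | no | no | no named item |
| Raised blood pressure | yes | yes | measured on its own schedule |
| Raised heart rate | yes | yes | measured on its own schedule |
| Nausea | yes | yes | yes |
| Headache | yes | yes | no |

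Counting blood pressure and heart rate separately, 4 of 4 physiological effects are solicited and 0 of 4 psychological effects are. Nausea is both a timed check and a solicited AE. Anxiety and distress are timed checks only.

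**Step 2. Where the collected data go**

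- *Timed checks (9.3.2).* Their stated use is to help Facilitators monitor the participant and alert the Study Physician. Neither document says when a positive check becomes an AE, and no safety endpoint in protocol 5.4.2 or SAP 3.4 uses them.
- *CEQ (5.5.6).* Completed at the end of dosing, classed as exploratory, in no safety endpoint, and outside the Clinical Study Report.
- *Unsolicited AEs (synopsis).* Anything else observed by staff or reported by the participant is recorded. Section 16.4.6 codes and tabulates all recorded AEs by SOC and preferred term. This route is open to anxiety and the rest, but only after someone judges the event to be an AE.
- *Preferred terms (18.1.1).* Psychosis, confusion, disorientation and similar terms are named for abuse-liability classification, at the PI's discretion. Anxiety, panic and delusion are not among them.
- *AE interviews (Table 1).* Scheduled on Days 0, 1, 8, 15 and 42. Neither solicited list gives them a prompt for the four effects.

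**Step 3. Can the size be calculated?**

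It cannot. An expected count needs a true incidence p and a capture proportion c, and the documents give neither. As an illustration on assumed values only, with n = 15 on psilocybin:

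- Expected recorded cases = n × p × c. With p from 20% to 40% and c from 50% to 100%, this runs from 15 × 0.20 × 0.50 = 1.5 to 15 × 0.40 × 1.00 = 6.
- Expected cases lost = n × p × (1 − c). This runs from 0 at full capture to 15 × 0.40 × 0.50 = 3.

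The range includes no loss at all. It shows what one or two discretionary recording decisions can do to an arm of 15; it does not estimate what will happen.

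**The case against.** A reader might infer that the psychological risk will be under-counted, or that the study report must show a benign profile by construction. The documents do not support that:

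- The unsolicited route includes events that staff observe, so capture does not depend only on a participant volunteering something.
- Observation during dosing is nearly continuous, anxiety and distress are checked at set times, and section 9.3.3 adds an assessment before release.
- AE interviews are scheduled, AEs are monitored from consent to end of study (18.5), and all recorded AEs are tabulated whether solicited or not.
- Five of the seven endpoints in 5.4.2 do not depend on the solicited list.
- The statement in 17.1.1 is qualified towards doses above 25 mg.
- The CEQ is an experience scale with no stated threshold for an AE, and its results are to be published.
- The eCRF and the Manual for Clinical Facilitators are not shown and may say how a positive check is recorded.

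All of this stands against a claim of certain under-counting. It does not remove the gap. The dose qualifier says where the effects are more marked and does not exclude them at 25 mg, which is the trial dose. The observation and checks produce data without a stated route into the AE record. Publishing the CEQ in a journal does not put it beside the other safety data in the study report.

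**Conclusion.** The point holds in limited form. The psychological effects ranked as most likely are on neither solicited list, although every physiological effect in the same section is. The two sources that address them directly, the timed anxiety and distress checks and the CEQ, reach no safety endpoint, and the CEQ does not reach the Clinical Study Report. The consequence is a risk of incomplete or uneven capture between arms, because recording rests on the judgement of staff and participants and Facilitators may be functionally unblinded. Under-counting is possible but not shown, and its size cannot be estimated from the documents. The conclusion assumes that no unseen document already turns a positive check into an AE by rule. The change is worth making because the data are already collected.

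**What to change.** 1. Add anxiety/panic, acute psychological distress, delusion/paranoia and confusion/cognitive impairment to the solicited AEs in the synopsis and in 18.1.3. Ask about them in the same words in both arms at the AE interviews already scheduled up to Day 8 (Days 0, 1 and 8).
2. State in 9.3.2 or 18.1 that each positive eCRF check of anxiety or distress is assessed and recorded as an AE.
3. Summarise those checks and the CEQ descriptively by arm with the safety data in the Clinical Study Report. The CEQ may stay exploratory and needs no AE threshold.
4. Reconcile the two solicited lists in the same edit. They differ on suicidal ideation, on substance misuse and overdose, and on the heart-rate definition (a duration in the synopsis, a need for medication in 18.1.3).

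The cost is a few extra prompts in existing interviews and one or two tables, with no new visit. The downside is that reported AE rates on psilocybin will be higher, and readers comparing with studies that did not solicit these effects should be told so.
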